### Plans to give access to the full protocol, participant level-data, and statistical code {31c}

The data sharing process will comply with the principles of good practice, and the data sharing will be conducted in accordance with the regulatory requirements.

## Oversight and monitoring

### Composition of the coordinating center and trial steering committee {5d}

Not applicable. There is no coordinating center and trial steering committee of this study.

### Composition of the data monitoring committee, its role and reporting structure {21a}

To guarantee the quality of this RCT, it will be carried out in a professional setting at the Shanghai Municipal Hospital of Traditional Chinese Medicine. We will promptly input the data on ResMan website. Working as the data monitoring team, the Clinical Research Center of Drugs of Shanghai University of TCM will identify problems in the trial, examine collected data, and control bias. A qualified clinical trial specialist will be invited to monitor this study.

### Adverse event reporting and harms {22}

Any adverse events related to the intervention will be reported by participants and practitioners. Details of each adverse event will be registered by the Scientific Research Supervision group of the Shanghai Municipal Hospital of Traditional Chinese Medicine and chronicled in a case report form. Adverse events include any symptoms or diseases that are unexpected throughout the duration of the RCT. All subjects in the trial will receive a certain amount of compensation.

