#### Acupuncture group

Participants will take the supine position while wearing an eye-patch. The right calf and abdomen will be uncovered sufficiently to expose the lower border of the right patella and the space between the navel and xiphoid process respectively. The infrared imaging device will be used to measure the infrared thermal spectrum for 10 min at a lens distance of 1 m from the subject’s abdomen. Subsequently, sagittal scanning will be performed with an abdominal probe placed slightly to the right of the inferior of border of the xiphoid process. The left lobe of the liver, the lower pancreas, the abdominal aorta, and the superior mesenteric artery will be used as anatomical reference points to locate the gastric antrum. From here, the frequency of gastric antrum contraction will be recorded for 10 min continuously.

After sterilizing the skin, ST36 will be punctured at the insertion point under the guidance of ultrasonography until the needle tip reaches the crural interosseous membrane. A qualified and experienced acupuncturist will perform needle manipulation including lifting, thrusting and rotating to obtain the appropriate needling sensations (*deqi* sensation). Then, the researchers will record the frequency of antral contraction for 10 min with the ultrasonic probes and conduct needle manipulation in the 5th minute. After wiping the ultrasound gel off the skin until it thoroughly dried, the researchers will collect infrared thermal spectrum data from the abdomen.

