## Assignment of interventions: blinding

### Who will be blinded {17a}

This is a single-blinded (participants-assessor-blinded) trial. Participants will be asked to wear an eye mask during the whole intervention in an enclosed space. All researchers except the acupuncturists and sonographer will be blind to the group assignment, including statisticians, outcome assessors, and data analysts. We will attempt to validate the successful implementation of the blinding method. All participants will be told that the presence or absence of acupuncture sensation is normal. Furthermore, all researchers will accept training on the RCT specification before the trial and will strictly adhere to the separation principle of each department.

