The key technical problems to be solved in this experiment are as follows: (1) the measurement of thermal infrared imaging is sensitive to ambient temperatures (2) to observe and guide the whole process of needling and obtain a legible ultrasound image of the needle body and (3) the application of the sham acupuncture method. The human skin surface temperature changes very little in a constant temperature environment. So, we will use a highly sensitive and accurate thermometer to monitor the room temperature in real time, in a closed space without convection gas or other extraneous heat source. It is necessary for the needle body to be perpendicular to the acoustic waves in order for optimal propagation. Only by using this orientation can we effectively guide the whole process of the needling. This means acupuncturists will need to penetrate into the skin at a point away from the routine insertion point. Nonetheless, we can also guarantee that the acupuncture area is located with precision. The acupuncturist and sonologist should be trained several times before the trial begins to ensure an effective implementation of the sham acupuncture technique and to be prepared to give reasonable explanations in case of doubts from sham acupuncture group participants.

There are some limitations in this randomized controlled trial. It is inevitable for acupuncturists to know when they are implementing the real or sham acupuncture treatment and its possible effects. To minimize suggestive bias from this limitation, we will ask all participants to wear an eye-mask. This trial is the primary study into the effect of a specific acupoint in relation to the *deqi* condition. In further studies, we may consider a multicenter clinical trial with patients. We expect that this study will provide more credible evidence for the effect of *deqi* sensations and the specificity of ST36 on gastric antrum contraction function and make up for the deficiency of current clinical trials focused on the methodology of acupuncture.

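### Reporting of intervention-related adverse events rests partly on practitioners who know the arm, so any safety description by arm may partly reflect that knowledge (minor)

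*Protocol article*

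**What the plan says.** Under *Adverse event reporting and harms {22}* the protocol article makes three statements:

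- Who reports: "Any adverse events related to the intervention will be reported by participants and practitioners".
- Who registers: "Details of each adverse event will be registered by the Scientific Research Supervision group of the Shanghai Municipal Hospital of Traditional Chinese Medicine", with the details entered in a case report form.
- What counts: "Adverse events include any symptoms or diseases that are unexpected throughout the duration of the RCT".

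Under *Who will be blinded {17a}* it says: "All researchers except the acupuncturists and sonographer will be blind to the group assignment, including statisticians, outcome assessors, and data analysts". The Discussion concedes the point for the needling staff: "It is inevitable for acupuncturists to know when they are implementing the real or sham acupuncture treatment and its possible effects".

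Participants are masked: "Participants will be asked to wear an eye mask during the whole intervention in an enclosed space". They are also told in advance what to make of sensations: "All participants will be told that the presence or absence of acupuncture sensation is normal". Under *Strategies to improve adherence {11c}* they may voice their feelings at any point in the session.

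Safety is among the stated purposes, in the Discussion paragraph of the abstract and in the third item of *Objectives {7}*. The abstract's Methods paragraph says that adverse events will be evaluated and recorded. They are not listed among the primary or secondary outcomes.

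**The concern.** Two features of the harms section work together.

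First, one of the two named sources of reports knows the arm. I read *practitioners* as the acupuncturists. If the word also covers the sonographer, the position is the same, since both roles are excepted from blinding.

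Second, the reporting sentence covers related events only. Someone therefore has to decide that an event is related before it enters the record, and for a practitioner's report that person knows whether the needling was deep with manipulation or shallow without it. The definition of an adverse event in the same section carries no such condition, so the two sentences describe different sets of events.

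At stake is the reading of any table of events by arm. The arms differ in depth and manipulation, so readers will look for a difference in local reactions. If capture differs by arm, such a table mixes true harm with reporting behaviour, and the two cannot be separated afterwards.

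**Working it through.** The article gives no adverse event rate, so there is no safety figure to reproduce. The check is a comparison of the passages, followed by an illustration.

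**Path of an event into the record**

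| Step | Who | Knows the arm? | Source |
|---|---|---|---|
| Reports, participant | Participant | No, masked in both arms | {17a}, {22} |
| Reports, practitioner | Acupuncturist | Yes | {17a}, Discussion, {22} |
| Judges relatedness before reporting | Not named; implied for whoever reports | Yes for practitioner reports | {22} |
| Registers details | Supervision group | Blinded, if counted among the researchers | {17a}, {22} |
| Confirms relatedness for compensation | Expert committee | Not stated separately | {30} |

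Registration comes after reporting, so blinding at that step cannot recover an event that a practitioner judged unrelated and did not report. The word *unexpected* in the definition also calls for a judgement, and the Discussion says that acupuncturists know the possible effects of each treatment.

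**Input from the document.** 58 per arm (*Sample size {14}*). This reproduces as (1.960 + 1.282)² × (0.7×0.3 + 0.4×0.6) / 0.3² = 52.54, and 52.54 × 1.1 = 57.8, so 58. Rounding to 53 and dividing by 0.9 gives 59. Nothing below depends on that difference.

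**Illustration 1: capture halved in one arm (assumed).** The true rate p is the same in both arms. The expected records are 58p and 58 × p/2. The last three columns give the chance that a two-sided 5% test would call the arms different. The first uses the normal approximation Φ((d − 1.96·se0)/se1). The other two sum the exact binomial probabilities over all pairs of counts.

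| True rate, both arms | Expected records | Normal approx. | Pearson chi-squared, exact sum | Fisher, exact sum |
|---|---|---|---|---|
| 5% | 2.9 v 1.45 | 10% | 9% | 2% |
| 10% | 5.8 v 2.9 | 17% | 17% | 8% |
| 20% | 11.6 v 5.8 | 32% | 33% | 24% |

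For the 10% row: d = 0.10 − 0.05 = 0.05. The mean rate is 0.075, so se0 = √(2×0.075×0.925/58) = 0.0489. se1 = √((0.10×0.90 + 0.05×0.95)/58) = 0.0487. Then (0.05 − 1.96×0.0489)/0.0487 = −0.94, and Φ(−0.94) = 0.17.

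**Illustration 2: what the blinded participant channel does (assumed).** Let practitioners capture 90% of events in one arm and 50% in the other. Let participants independently capture a share q, the same in both arms. Total capture is 1 − (1−q)(1−r), where r is the practitioner share. With a true rate of 10% there are 5.8 true events per arm.

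| q | Capture | Expected records | Ratio |
|---|---|---|---|
| 0 | 0.90 v 0.50 | 5.2 v 2.9 | 1.80 |
| 0.5 | 0.95 v 0.75 | 5.5 v 4.4 | 1.27 |
| 0.9 | 0.99 v 0.95 | 5.7 v 5.5 | 1.04 |

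The distortion shrinks as participants report more of the events themselves.

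**Direction.** It can also run the other way. With assumed true rates of 15% v 8% and capture of 50% v 90%, the record shows 58×0.15×0.50 = 4.4 v 58×0.08×0.90 = 4.2, which hides a near-doubling.

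**The case against.** The strongest case against is that the text supports much less than a reader might infer. Four stronger readings are tempting.

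- *Events reach the record only if someone volunteers them.* The harms section says who reports. It does not say that reports are unprompted, or that participants are not asked. How events are elicited is often left to the full protocol or the case report form, so this silence in a condensed article is no finding. Likewise, *Data management {19}* has a blinded assessor collecting data, and nothing excludes adverse events from that role.
- *All ascertainment depends on the arm.* The participant channel is blinded. The eye-patch, the advance message about sensations and the freedom to speak at any time apply to both arms. Under-reporting from those causes is not differential in itself. A masked participant can still report pain or faintness, and the mask is stated for the intervention only.
- *A planned safety test is biased.* No comparison of adverse events by arm is specified. *Statistical methods {20a}* names a chi-squared test for categorical data in general, and {20b} plans no additional analyses. The safety aim can also be read as anatomical, resting on ultrasound guidance.
- *The acupuncturist is the only person who knows the arm.* The sonographer does too.

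All four corrections stand. It is also fair to say that the Discussion already discloses the acupuncturist's knowledge as a limitation, and that the capture rates above have no source. The stated rule remains: related events, reported in part by staff who know the arm, beside a broader definition in the same section. That is something the article fixes, not a detail left out.

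**Conclusion.** The concern holds in limited form. Practitioner reports of adverse events come from people who know the arm, and the restriction to related events lets that knowledge act before registration. The restriction also sits uneasily with the broader definition beside it. Any description of safety by arm may therefore partly reflect knowledge of the arm.

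The size and direction cannot be derived from the documents. The illustrations show only that moderate differences in capture could create or hide a difference of a few events at 58 per arm. They also show that a well-working participant channel would remove most of it. They rest on assumed event rates, assumed capture rates and, in the second illustration, independent channels. The conclusion itself rests on reading *practitioners* as staff who know the arm. The primary outcome and the sample size are not touched. Minor priority.

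**What to change.** In *Adverse event reporting and harms {22}*:

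1. Record all adverse events regardless of relatedness, and assess relatedness afterwards as a separate item. This brings the reporting sentence into line with the definition.
2. After the participant has completed the C-MASS, have existing blinded data-collection staff ask every participant in both arms the same short set of questions on reactions. Identical questions also avoid a prior judgement of what is unexpected.
3. If the needling site is to be looked at, have it done by someone who does not read the ultrasound recordings, or after those readings are locked. *Outcomes {12}* has the ultrasound data measured from playback, so a visible reaction could hint at the arm before the primary outcome is read. Placing the look after the C-MASS does not by itself prevent this.
4. Report the solicited events by arm, and list practitioner-reported events separately.

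The cost is a short checklist, a few minutes per session and a small remaining risk that an answer or a visible reaction hints at the arm. Treatment, the primary analysis and the sample size do not change.

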**Methods:**

This is a two-arm, single-blind, randomized, controlled trial. A total of 116 acupuncture-naïve healthy subjects will be randomly allocated to the acupuncture group or sham acupuncture group in a 1:1 ratio. Participants in the acupuncture group will receive manual acupuncture at Zusanli (ST36) with the needling depth at crural interosseous membrane. Those in the sham acupuncture group will be given penetrating needling depth at the superficial fascia layer. The primary outcome will be the changes in antral contraction frequency (ACF) before and after acupuncture. The secondary outcomes will be the changes in the thermal infrared spectrum of gastric area skin, the antral contraction amplitude (ACA), the antral movement index (AMI), and the scores on the Chinese version of Massachusetts General Hospital Acupuncture Sensation Scale (C-MASS). The adverse events will be evaluated and recorded in detail.

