**Discussion:**

This study may provide visual and objective evidence regarding the safety and efficacy of manual acupuncture at Zusanli (ST36). In addition, the results of this study will help to identify the role of Zusanli (ST36)in the inducing *deqi*.

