### Objectives {7}

Participants who are in acupuncture with the *deqi* sensations group will experience more dramatic changes in the antral contraction frequency (ACF), antral contraction amplitude (ACA), and skin temperature of abdomen than those in the acupuncture group without *deqi* sensations.

The objectives include the following:
To determine the effects of ultrasound-guided acupuncture at ST36 on the antral contraction frequency, the antral contraction amplitude, and the skin temperature of the abdomen.To observe and analyze the relationship among the acupoint, the anatomical structure of acupoint area, and the antral contraction function in the  acupuncture group (with *deqi*) and sham acupuncture group (without *deqi*) respectively.To provide standardized and visualized experimental basis for improving the safety and effectiveness of clinical acupuncture techniques.

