#### Plans to promote participant retention and complete follow-up {18b}

Follow-up of subjects is not required in this study. This trial is an observation of the immediate effects of acupuncture intervention without involving any longer follow-up evaluation. We will collect ultrasound and infrared thermal imaging data before and after acupuncture intervention. Although participants who do not receive needling for any reason, their ultrasonic data of gastric antrum will also be collected, because we need to use ultrasound imaging technology to help determine whether the participants meet the inclusion criteria.

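### Adverse events are described by unexpectedness but reported by relatedness, so it is unclear whether foreseeable needling reactions will be recorded

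*Protocol article*

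**What the plan says.** The section on adverse event reporting and harms {22} makes three statements that bear on scope.

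- Reporting: "Any adverse events related to the intervention will be reported by participants and practitioners".
- Registration: "Details of each adverse event will be registered by the Scientific Research Supervision group", with entry in a case report form.
- Description of what counts: "Adverse events include any symptoms or diseases that are unexpected throughout the duration of the RCT".

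The Methods part of the abstract is broader: "The adverse events will be evaluated and recorded in detail".

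On timing, the section on retention and follow-up {18b} states "Follow-up of subjects is not required in this study" and explains why: "This trial is an observation of the immediate effects of acupuncture intervention without involving any longer follow-up evaluation".

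Safety is among the trial's stated purposes. The Discussion part of the abstract says "This study may provide visual and objective evidence regarding the safety and efficacy of manual acupuncture at Zusanli (ST36". The last of the listed objectives {7} is "To provide standardized and visualized experimental basis for improving the safety and effectiveness of clinical acupuncture techniques".

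**The concern.** Whether a harm is recorded should not depend on whether someone thought it likely beforehand, or on whether the person reporting it attributes it to the needle. Both are classifications to make after the event is on file. Here the only sentence saying what an adverse event is turns on unexpectedness, and the only sentence saying what is reported turns on relatedness.

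The events most at risk are ordinary needling reactions: they are foreseeable, so a strict reader of the description could leave them out. The two arms also differ in the features likely to cause them. An undercount could therefore be unequal between arms and shrink a true difference in harms, as well as lowering the total. What is at stake is the credibility of any statement on safety from this trial, not the analysis of antral contraction frequency.

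**Working it through.** The point rests on wording, so there is no plan figure to reproduce. The check sets the sections side by side.

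1. **Scope of the data.**

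| Place | Scope stated |
|---|---|
| {22}, description of adverse events | Symptoms or diseases that are unexpected |
| {22}, reporting sentence | Events related to the intervention |
| {22}, registration sentence | Each adverse event |
| Abstract, Methods | Adverse events, no limit |

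A related but foreseeable bruise falls under the second row and, read literally, not the first. An unexpected symptom thought unrelated falls under the first and not the second. The abstract would cover both. The article does not say which scope governs.

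2. **Difference between arms.** In the acupuncture group the needle tip reaches the crural interosseous membrane. The needle is lifted, thrust and rotated, then manipulated again in the 5th minute. In the sham group the tip goes no deeper than the superficial fascia, with no manipulation. The section on the ultrasonic anatomical diagram of ST36 measures the depth of the anterior tibial artery and deep peroneal nerve as important structures in this area. It is therefore plausible that bruising, bleeding and nerve symptoms are commoner in the acupuncture arm. That is an inference from the procedures; the article gives no rates.

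3. **What participants may regard as expected.** The main Discussion counts soreness and numbness among the deqi sensations. The blinding section {17a} says participants will be told that having or not having needling sensation is normal. A participant whose numbness lasts has thus been given a reason not to see it as unexpected.

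4. **Relatedness at the reporting stage.** Reports come from participants and practitioners {22}. Acupuncturists and the sonographer know the allocation {17a}. Limiting reports to related events gives knowledge of allocation a way to influence what is reported. It is also unnecessary, since the section on post-trial care {30} already has an expert committee confirm relatedness for compensation.

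5. **Collection window.** The description in {22} runs for the duration of the trial; {18b} requires no follow-up. Together they do not say when collection closes for a participant, or whether a reaction appearing after the session would be captured.

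**The case against.** The strongest reply is that nothing is expressly excluded. The description uses an inclusive verb, and unexpected may be loose wording for untoward. The reporting sentence, taken alone, covers a related haematoma or faint. The abstract carries no limit, and the discontinuation section {11b} refers to serious acupuncture-related reactions without requiring them to be unexpected. Participants may report their feelings at any time {11c}. The C-MASS collects 12 sensations in both arms, with a blank row for others. The safety objective can also be read as concerning ultrasound visualisation of technique and not an adverse event rate.

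Most of this stands, and it rules out several stronger readings that a reader might infer:

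- **Known needling harms are excluded.** The text does not say so, and a joint filter of related and unexpected is not stated. Loss of these events is a risk under a strict reading.
- **The unblinded acupuncturist judges relatedness.** Section {22} names who reports, not who decides causality. The only adjudicator named is the expert committee in {30}.
- **Reporting is spontaneous and stops with the session.** The method of elicitation is not described. Section {18b} explains the immediate-effect design and sets no adverse event rule. Checklists, grading and tables by arm may sit in the full protocol or analysis plan, so their absence from the article is no finding.
- **The defect can be sized by the rule of three.** With 58 in the acupuncture arm, zero events give an upper 95% bound of about 3/58 = 5.2%. That bound depends on arm size alone and would be the same under a perfect definition.

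The reply does not reconcile the differing scopes in {22} and the abstract. Nor does the C-MASS fill the gap: it rates sensations at the end of the session and does not record signs such as bruising, or symptoms that persist afterwards.

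**Conclusion.** The concern holds as an inconsistency that should be corrected. Section {22} describes adverse events by unexpectedness and reports them by relatedness, while the abstract promises recording without either limit. Under a strict reading, foreseeable needling reactions could be missed, possibly more often in the acupuncture arm, and the relatedness condition brings practitioners who know the allocation into the reporting step. This weakens the safety evidence suggested in the abstract and, less directly, the safety objective.

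The size of any undercount is unknown. The conclusion rests on two assumptions: that staff could apply the wording of {22} literally, and that deeper, manipulated needling produces more of these reactions than superficial needling. The first depends on working documents not shown; the second is plausible from the described procedures but has no figure behind it. The efficacy inference is unaffected.

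**What to change.** Reword {22} so that every untoward symptom or sign after needle insertion is recorded, in the same way in both arms, whether or not it was expected or is thought related. Classify relatedness and expectedness afterwards; the expert committee already named in {30} could do this. State when collection starts and ends for each participant, and bring the abstract and {22} into line.

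If the definition and window are left as they are, limit the safety statement in the abstract's Discussion to what was observed during the session.

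The cost is a few sentences. The small downside is that more minor events will be recorded and need classifying.
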